### Randomization

Randomization will be carried out in two steps. First, 140 patients will be allocated into four group equally with simple concealed randomization; second, 15 patients will be randomly selected from each group to undergo MRI and PET-CT scans. To avoid bias caused by researchers’ subjective factors, randomization will be implemented by a third-party professional statistician using computer-generated randomization digital table which is created by SAS 9.2 (SAS Institute Inc., Cary, NC, USA). When participant-recruiting staff decides to recruit an eligible FC patient, they will send the patient’s name, gender, age, and telephone numbers to this statistician via a short message. The randomized result will then be put into an opaque envelope and delivered to the acupuncturists.

### Blinding

It is difficult to blind acupuncturists and patients in this trial for different types of interventions. However, it is feasible to confuse outcome assessors and statistical analysts. Patients are told that they will receive one of three effective interventions randomized after enrolment; during the acupuncture treatment, patients in groups A and group B will be separated into cubicles to refrain from communication. Outcome assessors and statistical analysts will be blind to the procedure and results of randomization, group allocation, and intervention.

### Control

We choose conventional medicine (PEG 4000) as a positive control to evaluate the therapeutic effects of acupuncture and select the sham acupuncture as a control to re-identify the specific effects of acupoints. To preclude the interference of self-healing tendency of FC, a waiting-list group is also designed.

### Intervention

#### Group A

Patients in this group will receive manual acupuncture at six verum acupoints (VA) (bilateral Zusanli [ST36], Tianshu [ST25], and Shangjuxu [ST37] (Fig. 3)) with disposable sterile filiform needles (0.25 × 40 mm, Huatuo Medical Instrument Co., Ltd., China). These acupoints have been proven effective and crucial in managing gastrointestinal disorders [16, 32]. Needles will be perpendicularly inserted into acupoints at a depth of 20–30 mm after skin disinfection using alcohol; acupuncturists will then bi-directionally twist needles by 90°–180°, lifting and thrusting needles with the amplitude of 3–5 mm for 1–1.5 Hz to induce *deqi* sensation (including soreness, numbness, distention, and heaviness). After the *deqi* sensation is attained, needles will be retained at the acupoints for 30 min. During the 30 min, the above procedures will be manipulated for 10–15 s every 10 min to maintain the *deqi* sensation. Patients will receive a total of 10 sessions of acupuncture in two weeks with five sessions per week (once a day for five days, followed by a two-day interval).

**Fig. 3 Fig3:**
[figure not shown]
Locations of acupoints and sham acupoints (SA). ST36 (Zusanli), on the anterior lateral side of the shank, 3 *cun* below ST35 (Dubi), one horizontally placed finger distance lateral to the anterior border of the tibia. ST37 (Shangjuxu), on the anterior lateral side of the shank, 6 *cun* below ST35 (Dubi), one horizontally placed finger distance lateral to the anterior border of the tibia. ST25 (Tianshu), on the middle portion of the abdomen, 2 *cun* lateral to the center of the navel. SA1, 1 *cun* outside of Zusanli (ST36) (between the Stomach Meridian and the Gallbladder Meridian), SA2, 1 *cun* outside of Shangjuxu (ST37) (between the Stomach Meridian and the Gallbladder Meridian), and SA3, 1 *cun* outside and above of Tianshu (ST25) (between Stomach Meridian and Spleen Meridian)

#### Group B

Patients in group B will receive 10 sessions of manual acupuncture at six sham acupoints (SA) (Fig. 3). Patients in this group will undergo an acupuncture procedure similar to the patients in group A, but no needle manipulation is performed after needle insertion and *deqi* sensation is not required.

All the acupuncture manipulation will be performed by two licensed acupuncturists with at least three years of clinical experience.

#### Group C

Patients assigned to this group will receive conventional medication, the PEG, which has been recommended in some guidelines and has been widely used in the digestive department for its definite efficacy and relatively few side effects [9, 33–35]. Patients will take 10 mg PEG 4000 powder (forlax©) (Ipsen Pharma, France) dissolved with 200–250 mL water once a day before bedtime for 10 days over a period of two weeks. In order to be consistent with the process of acupuncture treatment, oral medicine will also be taken over five consecutive days followed by a two-day interval. After treatment, patients will be required to return any untaken drugs to monitor the adherence.

#### Group D

During the treatment period, no intervention will be performed on this group; however, it has been promised that these participants will receive 10 sessions of acupuncture therapy at the end of the trial, similar to the participants in group A.

Participants with fainting, infection, severe diarrhea, dehydration, or other severe adverse events should be discontinued from treatment and processed immediately. During the treatment period, participants are usually not allowed to use concomitant care and interventions. However, if required, participants will be permitted to use extra osmotic laxatives; the type and dosage of medication used should be recorded in the case report form (CRF). If patients take concomitant care and interventions more than three times in the treatment period, they will be defined as non-adherent and will not be enrolled into the statistical analysis.

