## Method and Design

### Study design

This is a multimodal neuroimaging RCT. A total of 140 eligible FC patients diagnosed with the Rome IV diagnostic criteria [26] will be recruited and randomized to four groups with a 1:1:1:1 ratio. Fifteen participants in each group will be randomly selected to undergo both MRI and PET-CT scans. Outcome assessments will be performed at three timepoints: baseline; mid-point; and the end of treatment/waiting (see Fig. 1 for a detailed study schedule).

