### Data analysis

#### Clinical data analysis

The clinical data will be analyzed using SPSS 20.0 statistics software (IBM Co., Armonk, NY, USA) based on the per-protocol (PP) principle. Continuous variables on normal distribution will be described with means and standard deviation (SD). Continuous variables conforming to a skewed distribution will be described with median and inter-quartile range. Categorical variables will be described with percentages (%).

Clinical data from the four groups will be compared using one-way ANOVA; statistical analysis between two groups (group A and B, group A and C, group A and D) will be performed using Dunnett’s test. The comparison between baseline and end of treatment in each group will be carried out with a paired samples *t*-test. The clinical outcome stool diary and CCS scores will be compared at three timepoints using the repeated measures ANOVA. Clinical data on skewed distribution will be compared using a non-parametric test. Categorical variables will be compared using the *χ*^2^ test or Fisher’s exact test. The statistical significance threshold is set at 0.05 with the two-sided test.

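### The only stated clinical analysis is per-protocol and removes patients for repeated use of permitted extra care, a post-randomisation event likely to be related to response and to differ by arm

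*Protocol article*

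**What the plan says.** Under Clinical data analysis, the protocol article states that the clinical data will be analysed "based on the per-protocol (PP) principle". Neither that section nor any other names an intention-to-treat, full-analysis or sensitivity population.

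The exclusion rule is in the last paragraph under Group D. That paragraph speaks of participants in general, so I read it as applying to all four arms. Other care is normally not allowed during treatment, but "if required, participants will be permitted to use extra osmotic laxatives", with type and dosage entered in the CRF. The rule follows: "If patients take concomitant care and interventions more than three times in the treatment period", then "they will be defined as non-adherent and will not be enrolled into the statistical analysis".

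Three features of the design bear on who will meet this rule:
- Blinding: "It is difficult to blind acupuncturists and patients in this trial for different types of interventions".
- Waiting list (Group D): "During the treatment period, no intervention will be performed on this group".
- Group C receives PEG 4000, itself an osmotic laxative, as its assigned treatment.

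Patients are "randomized to four groups with a 1:1:1:1 ratio", and the first aim in the Background is to test efficacy by comparing verum acupuncture with sham acupuncture and PEG 4000.

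**The concern.** Care that the protocol permits becomes a reason for removal after randomisation. In a constipation trial, the patients who reach for a laxative again and again are likely to be those whose bowels respond poorly. Removing them raises the mean improvement of those left in each arm, and raises it more where more are removed. Randomisation balances the arms as allocated, not the subsets left after such a rule. The planned ANOVA and Dunnett's tests take the remaining patients as given and cannot undo the selection.

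What is at stake is every clinical comparison under the first aim, and the correlations between imaging and symptom change if the rule is applied to the scanned patients too. The trial is framed as a comparison of effect with no non-inferiority margin, so the article offers no reason for per-protocol to stand alone.

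**Working it through.** **1. The plan's own figure.** Inputs from Sample size: mean weekly SBM improvement 2.5 (verum, A), 1.8 (sham, B), 2.2 (PEG 4000, C), 0.9 (waiting list, D); SD 2.0; α 0.05; power 0.80. For a one-way ANOVA with n per arm, the noncentrality is n × Σ(mean − grand mean)² / SD². The grand mean is 1.85 and the sum of squares 1.45, so the noncentrality is 0.3625n. At n = 32 it is 11.6 and power is 0.813; at n = 31 power is 0.799. The stated 128 = 4 × 32 reproduces.

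**2. Bias when exclusion is correlated with poor response.** Let response and laxative propensity be bivariate normal with correlation ρ between propensity and poor response, and let the proportion p with the highest propensity be excluded. The mean of those who remain rises by

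shift = ρ × SD × φ(z_p) / (1 − p),

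where φ is the standard normal density and z_p the p-quantile. The ratio φ(z_p)/(1 − p) is:

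| p | 5% | 10% | 15% | 30% |
|---|---|---|---|---|
| ratio | 0.109 | 0.195 | 0.274 | 0.497 |

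Assumed, because the article gives no rates: ρ 0.3-0.7; 5-10% excluded in verum; 15-30% in the comparator. Only the SD of 2.0 and the planned differences come from the document.

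- Largest distortion (ρ 0.7, 5% v 30%): 0.7 × 2.0 × (0.497 − 0.109) = 0.54. A-D: 1.6 − 0.54 = 1.06. A-B: 0.7 − 0.54 = 0.16.
- Smallest distortion (ρ 0.3, 10% v 15%): 0.3 × 2.0 × (0.274 − 0.195) = 0.05. A-D: 1.55. A-B: 0.65.

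If the exclusion rates are swapped so that verum loses more, the same amounts are added: A-B runs from 0.75 to 1.24 and A-D from 1.65 to 2.14.

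**3. A second model.** Suppose instead that patients whose improvement falls below a cut-off c are the ones dropped. The remaining mean is m + 2φ(a)/(1 − Φ(a)), with a = (c − m)/2.

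| c (SBM/week) | excluded A / B / D | A-B (planned 0.70) | A-D (planned 1.60) | A-C (planned 0.30) |
|---|---|---|---|---|
| −2 | 1% / 3% / 7% | 0.63 | 1.36 | 0.28 |
| −1 | 4% / 8% / 17% | 0.55 | 1.17 | 0.25 |
| 0 | 11% / 18% / 33% | 0.46 | 0.94 | 0.20 |

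**4. Equal true means.** If the worst 5% are dropped in one arm and the worst 15-25% in the other, a false difference of 0.33-0.63 SBM/week appears, close to the planned verum-sham effect of 0.7.

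**5. Power, before any bias.** Under the planning inputs, 35 per arm gives 0.851. Dropping 10%, 20% or 30% of the 140 gives 0.806, 0.751 or 0.685 (assumed rates).

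Steps 2-4 treat the recorded improvement as unaffected by the extra laxative. They show how selection works and do not forecast the trial's result.

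**The case against.** The strongest defence is that the rule acts on use of other care, not on the outcome, and may touch few patients. Both halves have force. A reader might infer that patients are removed because of their measured result. The text does not say so: it counts uses of concomitant care, which can include care unrelated to the bowel, so it is a proxy for poor response. And where few exceed three uses the effect is slight: with 1% v 3% excluded in step 3, A-B moves only from 0.70 to 0.63. Neither half makes the remaining groups the randomised ones.

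It can also be said that if waiting list and sham lose more patients, the rule works against verum and is conservative. That is plausible for A-B and A-D, but the direction is not established by the document, and with unblinded patients it could be the reverse.

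Two further inferences are tempting and not supported. One is that these exclusions come on top of the 10% drop-out allowance: Sample size does not say what that allowance covers, and it may include them. The other is that movements produced by extra laxatives will be counted as spontaneous: the article names weekly SBMs without an operational definition, which a condensed article can leave to the full protocol.

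An appeal to an unseen analysis plan does not help, because the article itself fixes both the per-protocol principle and the exclusion rule.

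**Conclusion.** The point holds. Per-protocol as the only clinical analysis, combined with removal for repeated use of permitted care, can bias the verum comparisons in either direction.

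The size cannot be known from the document. Under the assumptions of step 2, the distortion is about 0.05 to 0.54 SBM/week. The upper end is most of the planned verum-sham difference of 0.7 and about a third of the planned verum-waiting list difference of 1.6. The result rests on three conditions: that laxative use is related to poor response, that it differs by arm, and that enough patients pass three uses. The first two are plausible from the design; the third is unknown. This should be corrected before analysis, since diary data not collected from such patients cannot be recovered later.

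**What to change.** - Make the primary clinical analysis all randomised patients in their assigned group, including those who used extra laxatives or other care and those who stopped treatment.
- Use all available diary data, and go on collecting the diary from these patients to the end of the treatment or waiting period.
- Keep the per-protocol set, with the more-than-three-uses rule, as a supportive analysis.
- Report extra-laxative use by arm from the type and dosage already recorded in the CRF.

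I would not add a rule that discounts movements attributed to extra laxatives. The article lists type and dosage but not dates, and in the PEG 4000 arm such movements are hard to separate from those due to the assigned treatment. The repair does not need it.

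The cost is wording in the analysis section, one extra analysis and continued diary collection. Trial status reports 26 patients included, so most of the collection still lies ahead. The estimated effect may move in either direction. No rule on patient care changes.

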### Multimodal data acquisition

#### MRI data acquisition

The morning after an overnight fast, participants will undergo a MRI scan with a 3.0-T MR scanner (Siemens AG, Germany) at Huaxi Magnetic Resonance Research Center, West China Hospital of Sichuan University, Chengdu, China. The scanning procedure contains a localizer, a high-resolution three-dimensional T1-weighted imaging (3D-T1WI), a blood oxygenation level-dependent fMRI (BOLD-fMRI) and a diffusion tensor imaging (DTI) sequence. The 3D-T1WI scanning parameters will be as follows: repetition time (TR)/echo time (TE) = 1900/2.26 ms; slice thickness = 1 mm; slice number = 30; matrix size = 128 × 128; and field of view (FOV) = 256 × 256 mm. The BOLD-fMRI scanning parameters will be as follows: TR/TE = 2000/30 ms; flip angle = 90°; slice number = 30; matrix size = 128 × 128; FOV = 240 × 240 mm; slice thickness = 5 mm; and total volume = 240. The DTI data will be acquired with the following parameters: FOV = 240 × 240 mm; TR/TE = 6800/93 ms; matrix size = 128 × 128; and slice thickness = 3 mm with no gap. Two diffusion-weighted sequences were acquired using gradient values b = 1000 s/mm^2^ and b = 0 with the diffusion-sensitizing gradients applied in 64 non-collinear directions.

#### PET-CT data acquisition

The PET-CT scan will be performed after the MRI scan at the PET-CT center of Sichuan Provincial People’s Hospital, Chengdu, China. The scan will be executed with the Biograph Duo BGO scanner (Siemens AG, Germany) and fluorine-18-fluorodeoxyglucose (^18^F-FDG, radiochemical purity > 95%, 0.11 mCi/kg) will be selected as the tracer. In the scanning period, CT images will be acquired firstly with the parameters as follows: voltage = 120 KV; current = 120 mAs; matrix size = 256 × 256; magnification = 2×; and slice thickness = 3 mm. Then, PET performed with the parameters as follows: bed = 1; model = 3D; slice thickness = 3 mm; slice interval = 2.5 mm; matrix size = 256 × 256; scanning time = 8 min; and total counts = 3 × 10^9^. See Additional file 2 for the detailed MRI and PET-CT scanning process.

### Outcomes

#### Stool diary

The stool diary contains three domains: weekly SBMs; stool feature; and straining sensation. The stool feature is measured by the Bristol Stool Form Scale (BSFS) [36], which classifies the form of human feces into seven types from separate hard lumps (type 1) to entirely liquid (type 7). Straining sensation measured in the range of 0–3 represents the intensity of difficulty during defecation, “0” means no difficulty, “1” means slight difficulty, “2” means medium difficulty, and “3” means much difficulty and assisted measures are needed for defecation.

#### Cleveland Constipation Score (CCS)

The CCS [37] is a designated scale to evaluate patients’ gastrointestinal or anorectal symptoms. The CCS is composed of eight items: defecation frequency; straining feeling; incomplete feeling; abdominal pain; defecating time; assisted measures to defecation; unsuccessful defecation frequency in 24 h; and course of constipation. Each item is scored in the range of 0–4 or 0–2; the summation is in the range of 0–30. A higher score indicates more severe symptoms of constipation.

#### Patient Assessment of Constipation Symptom (PAC-SYM) and Patient Assessment of Constipation Quality of Life Questionnaire (PAC-QoL)

The PAC-SYM [38] is a self-rating scale to assess patients’ constipation symptoms in the last two weeks. It involves three aspects of symptoms (stool symptoms, rectal symptoms, and abdomen symptoms) and each symptom is scored in the range of 0–4 according to severity (“0” means not at all severe, “4” means very severe).

The PAC-QoL [39] is intended to reflect the QoL of FC patients in the last two weeks. It embodies seven dimensions with a total of 28 questions involving physical discomfort, social discomfort, psychological discomfort, anxiety and concern, and satisfaction in daily life. There are five options for each question in the range of 1–5 (“1” indicates no discomfort or feeling very satisfied, “5” indicates extreme severity and always appears or feeling very dissatisfied). A higher score of the PAC-SYM and PAC-QoL suggests more severe symptoms, more discomfort, less satisfaction, and poorer QoL.

#### Self-rating Anxiety Scale (SAS) and Self-rating Depression Scale (SDS)

Anxiety and depression are emotional disorders commonly accompanied by FGIDs [40]. Hence, the SAS [41] and SDS [42] are used to assess the emotional health of FC patients.

In addition, the heart rate variability (HRV) will be measured by dynamic electrocardiogram to evaluate the activity of the autonomic nervous system of FC patients [14].

The above outcomes will be assessed at baseline and at the end of treatment/waiting. In addition, the stool diary and CCS will also be evaluated at mid-point. The expectation for efficacy in each patient will be evaluated at baseline.

All the outcome assessments will be performed by independent outcome assessors. These assessors are trained before participating in this trial and blinded to the randomization.

### Data management

Clinical data will be managed with printed and electronic CRFs. Only outcome assessors have access to CRFs and will perform double-data entry. The Evidence-based Medicine Center of the CDUTCM will be responsible for monitoring the study and data every three months and will make the final decision to terminate the trial.

### Data analysis

#### Clinical data analysis

The clinical data will be analyzed using SPSS 20.0 statistics software (IBM Co., Armonk, NY, USA) based on the per-protocol (PP) principle. Continuous variables on normal distribution will be described with means and standard deviation (SD). Continuous variables conforming to a skewed distribution will be described with median and inter-quartile range. Categorical variables will be described with percentages (%).

Clinical data from the four groups will be compared using one-way ANOVA; statistical analysis between two groups (group A and B, group A and C, group A and D) will be performed using Dunnett’s test. The comparison between baseline and end of treatment in each group will be carried out with a paired samples *t*-test. The clinical outcome stool diary and CCS scores will be compared at three timepoints using the repeated measures ANOVA. Clinical data on skewed distribution will be compared using a non-parametric test. Categorical variables will be compared using the *χ*^2^ test or Fisher’s exact test. The statistical significance threshold is set at 0.05 with the two-sided test.

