**Methods:**

This is a multimodal neuroimaging randomized controlled trial. In total, 140 FC patients will be randomly allocated into four groups: the verum acupuncture group; the sham acupuncture group; the PEG 4000 group; and the waiting-list group. This trial will include a two-week baseline period and a two-week treatment period. Patients will receive 10 sessions of acupuncture, sham acupuncture, PEG 4000, or no intervention during the treatment period. The stool diary, Cleveland Constipation Score (CCS), Patient Assessment of Constipation Symptom (PAC-SYM), and Patient Assessment of Constipation Quality of Life Questionnaire (PAC-QoL) will be used to assess the clinical efficacy of different interventions. The MRI and PET-CT scans will be performed to detect cerebral functional changes in 15 patients in each group at baseline and at the end of treatment/waiting. Multimodal imaging data will be associated with clinical data to investigate possible correlation between brain activity changes elicited by different interventions and symptoms improvement.

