### Sample size

According to a previous systematic review [29] that compared the therapeutic effects of acupuncture, lactulose, and sham acupuncture for FC, the mean weekly improvement in SBMs of 2.46, 2.17, and 1.76 were found in the verum acupuncture, lactulose, and sham acupuncture group, respectively. We anticipate a mean weekly SBM improvement of 2.5 in the verum acupuncture group, 2.2 in the PEG 4000 group, 1.8 in the sham acupuncture group, and 0.9 in the waiting-list control group. Considering α = 0.05, 1-β = 0.8, and a standard deviation of 2.0, a sample size of 128 is needed, with a drop-out rate of 10%; a total of 140 FC patients will be finally recruited.

Based on previous neuroimaging studies [30, 31], 12–15 individuals in each group is the reasonable sample size for stable cerebral responses. Therefore, in this trial, 15 participants randomly selected from each group will be scanned by MRI and PET-CT.

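### The between-group ANOVA, Dunnett contrasts and repeated-measures ANOVA are valid but use no baseline covariate and so lose precision; the within-group paired t-tests do not test a treatment effect

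*Protocol article*

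**What the plan says.** The section Clinical data analysis of the protocol article names three procedures for continuous outcomes.

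- Between groups: "Clinical data from the four groups will be compared using one-way ANOVA", followed by "statistical analysis between two groups (group A and B, group A and C, group A and D) will be performed using Dunnett’s test". No covariate is named, and the text does not say whether the response is the end-of-treatment value or the change from baseline.
- Within groups, a t-test is planned: "The comparison between baseline and end of treatment in each group will be carried out with a paired samples".
- Over time: "The clinical outcome stool diary and CCS scores will be compared at three timepoints using the repeated measures ANOVA".

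Baseline is one of those times. Under Study design, "Outcome assessments will be performed at three timepoints: baseline; mid-point; and the end of treatment/waiting". The baseline data are collected in any case: the abstract says "This trial will include a two-week baseline period and a two-week treatment period", and the Outcomes section has all outcomes assessed at baseline and at the end. Skewed outcomes go to a non-parametric test. The Sample size section plans on these mean weekly gains in spontaneous bowel movements: "2.5 in the verum acupuncture group, 2.2 in the PEG 4000 group, 1.8 in the sham acupuncture group, and 0.9 in the waiting-list control group". The SD assumed there is 2.0.

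**The concern.** Three separate matters arise.

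1. A one-way ANOVA has one factor and no covariate. Whichever response is used, it leaves in the error term variation that the measured baseline could remove. Chance baseline imbalance is also not removed efficiently: not at all with end values, and over-corrected with change scores when r is below 1 and the variances are equal.
2. Randomisation makes the expected group difference at baseline zero. Counting baseline as an outcome time therefore adds a time point that carries no treatment effect.
3. A paired t-test inside an arm tests whether that arm changed, not whether treatment changed it. The Control section includes the waiting list to account for spontaneous recovery. A test within one arm cannot separate that recovery from a treatment effect.

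At stake are precision in a trial whose verum–sham difference is small relative to its SD, and a set of p-values, at the same 0.05 threshold as the group comparisons, that could be misread as evidence of efficacy.

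**Working it through.** **Inputs from the article.** Mean improvements: A 2.5, C 2.2, B 1.8, D 0.9. SD 2.0, α = 0.05 two-sided, 128 evaluable patients in four equal arms, so 32 per arm.

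**Assumption.** The correlation r between baseline and later values is not given. I use 0.3, 0.5 and 0.7, with equal variances over time.

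**Step 1: the plan's own figure.** The mean of the four improvements is 1.85. The squared deviations sum to 0.4225 + 0.1225 + 0.0025 + 0.9025 = 1.45. The noncentrality of the omnibus F test is n × 1.45 / 2.0², which is 11.6 at n = 32. Power is 81.3% at 32 per arm and 79.9% at 31, so 128 reproduces as an omnibus ANOVA without covariate.

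**Step 2: gain from ANCOVA on the end value.** With σ² the variance of a single value, the error variance is σ² for end values, 2(1−r)σ² for change scores and (1−r²)σ² for ANCOVA. The ANCOVA ratio is therefore 1−r² against end values and (1+r)/2 against change scores. Both are below 1 for any r between 0 and 1.

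| r | ANCOVA / end-value variance | Omnibus power if 2.0 is the SD of end values | ANCOVA / change-score variance | Omnibus power if 2.0 is the SD of change |
|---|---|---|---|---|
| 0.3 | 91% | 81% → 85% | 65% | 81% → 95% |
| 0.5 | 75% | 81% → 92% | 75% | 81% → 92% |
| 0.7 | 51% | 81% → 98.5% | 85% | 81% → 88% |

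**Step 3: verum versus sham.** The difference is 2.5 − 1.8 = 0.7. Unadjusted, 0.7 / (2.0 × √(2/32)) = 1.40, so power is about 29% before multiplicity adjustment (normal approximation). With ANCOVA at r = 0.3/0.5/0.7 it is 31/37/50% if 2.0 is the SD of end values, or 41/37/33% if it is the SD of change.

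**Step 4: repeated measures with baseline as an outcome time.** Assume SD 2.0 at each time, compound symmetry and the full 0.7 difference already present at mid-point. The group main effect averages (0 + 0.7 + 0.7)/3 = 0.47; a smaller mid-point effect makes it smaller still. The relevant SDs are:

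- group main effect over three times: 2√((1+2r)/3)
- interaction contrast (mean of the two post-baseline values minus baseline): 2√(1.5(1−r))
- ANCOVA on the mean of the two post-baseline values: 2√((1+r)/2 − r²)

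Power for A versus B at 32 per arm (noncentral t, 62 degrees of freedom):

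| r | Main effect (0.47) | Interaction contrast (0.7) | ANCOVA (0.7) |
|---|---|---|---|
| 0.3 | 24% | 27% | 45% |
| 0.5 | 20% | 36% | 50% |
| 0.7 | 18% | 54% | 63% |

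**Step 5: paired t-tests.** If 2.0 is the SD of change, the noncentrality is mean / (2.0/√32), with 31 degrees of freedom. For the waiting list, 0.9 / 0.354 = 2.55 gives a 69% chance of significance. For sham, 1.8 / 0.354 = 5.09 gives 99.9%. If 2.0 is instead the SD of end values, the SD of change is 2.0 × √(2(1−r)). Over r = 0.3 to 0.7 the chances are then 55% to 89% for the waiting list and 98.6% to above 99.9% for sham.

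**The case against.** The best defence has four parts.

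- **The ANOVA may already use baseline.** A reader might infer that the baseline data are discarded. The article does not establish that: the sample size is set on improvement, so a change-score ANOVA is a natural reading. In that case baseline is used, only less efficiently. This stands, and it is why Step 2 covers both readings; ANCOVA is more precise under each.
- **ANOVA with Dunnett contrasts is a sound randomised comparison.** It matches the sample-size calculation and reaches its planned omnibus power without a covariate. This also stands. The point is an available gain in efficiency, not an invalid test, and its size depends on an r that the article does not report.
- **The repeated-measures analysis need not test the group main effect.** A reader might infer that the shrinkage from 0.7 to 0.47 is built into the plan. It is not: the article names neither the main effect nor the group-by-time interaction, and the interaction avoids that shrinkage. What remains is that the interaction contrast is still less powerful than the baseline-adjusted analysis in Step 4.
- **Efficacy is to be judged between groups.** A reader might infer that the whole plan makes sham and waiting list look effective. Only the paired t-tests could do so. The first aim is framed as a comparison of verum with sham and PEG 4000, and nowhere does the article say that efficacy will be concluded from the paired tests. They are, however, listed as tests with no descriptive label.

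Loss of patients with an incomplete series is a missing-data question that an analysis plan may settle, and it forms no part of this point.

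**Conclusion.** The point holds as a recommendation on efficiency and on the status of the within-group tests. The planned group comparisons are valid. For every r assumed from 0.3 to 0.7 they are less precise than ANCOVA, whichever response is meant, and the lost precision is worth about 4 to 17 percentage points of omnibus power (81% to between 85% and 98.5%). Using baseline as a third outcome time costs further power for verum versus sham under the assumptions of Step 4, more if the main effect is tested than if the interaction is. The paired t-tests answer no question about treatment and would more likely than not be significant in the untreated arm if the protocol's assumptions hold.

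It would go too far to say that adjustment makes the verum–sham comparison adequate. The end-value ANCOVA reaches 50% power at best before multiplicity adjustment, so that weakness is one of sample size.

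**What to change.** Three changes of wording in the analysis section:

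1. For approximately normal outcomes, replace the one-way ANOVA with an ANCOVA of the end-of-treatment value on group and that outcome's own baseline. Take the A–B, A–C and A–D contrasts from this model with Dunnett adjustment.
2. For stool diary and CCS, replace the three-time repeated-measures ANOVA with a mixed model that has mid-point and end values as outcomes and baseline as covariate.
3. Report change within each group as a mean with confidence interval, described as descriptive and not as a test of efficacy.

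Keep the planned non-parametric route for skewed outcomes. The cost is small: no new data or visits are needed, and SPSS fits these models. The Trial status section reports 26 patients included out of 140 planned, so at that stage the change could still be specified before any unblinded analysis.
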